# Prostate cancer–Exercise and Metformin Trial (Pre-EMpT): study protocol for a feasibility factorial randomized controlled trial in men with localised or locally advanced prostate cancer

**DOI:** 10.1186/s40814-022-01136-7

**Published:** 2022-08-12

**Keywords:** Prostate cancer, Metformin, Physical activity, Feasibility randomised controlled trial, Localised, Locally advanced, Radiotherapy, Prostatectomy, Active surveillance

## Abstract

**Background:**

Evidence from observational studies have shown that moderate intensity physical activity can reduce risk of progression and cancer-specific mortality in participants with prostate cancer. Epidemiological studies have also shown participants taking metformin to have a reduced risk of prostate cancer. However, data from randomised controlled trials supporting the use of these interventions are limited. The Prostate cancer–Exercise and Metformin Trial examines that feasibility of randomising participants diagnosed with localised or locally advanced prostate cancer to interventions that modify physical activity and blood glucose levels. The primary outcomes are randomisation rates and adherence to the interventions over 6 months. The secondary outcomes include intervention tolerability and retention rates, measures of insulin-like growth factor I, prostate-specific antigen, physical activity, symptom-reporting, and quality of life.

**Methods:**

Participants are randomised in a 2 × 2 factorial design to both a physical activity (brisk walking or control) and a pharmacological (metformin or control) intervention. Participants perform the interventions for 6 months with final measures collected at 12 months follow-up.

**Discussion:**

Our trial will determine whether participants diagnosed with localised or locally advanced prostate cancer, who are scheduled for radical treatments or being monitored for signs of cancer progression, can be randomised to a 6 months physical activity and metformin intervention. The findings from our trial will inform a larger trial powered to examine the clinical benefits of these interventions.

**Trial registration:**

Prostate Cancer Exercise and Metformin Trial (Pre-EMpT) is registered on the ISRCTN registry, reference number ISRCTN13543667. Date of registration 2nd August 2018–retrospectively registered. First participant was recruited on 11th September 2018.

## Background

Prostate cancer is the second commonest cause of UK male cancer death after lung cancer: in 2016, over 11,500 men died as a result of the disease [1]. While 10-year prostate cancer survival in England is high at 78% [1], prostate cancer mortality accelerates after 15 years [2, 3]. Furthermore, men undergoing treatment for early prostate cancer experience adverse effects (e.g. urinary incontinence, sexual dysfunction, fatigue and psychological impacts) [4] and one in three face biochemical recurrence [5]. These data suggest that there may be potential benefits of tertiary prevention interventions (e.g. rehabilitation programs) as an adjunct to primary treatment on long-term mortality and quality of life.

Observational studies suggest that men with prostate cancer who undertake moderate to vigorous physical activity have a reduced risk of biochemical recurrence and mortality from prostate cancer [6, 7]. Specifically, Kenfield et al. [7] observed an inverse association between brisk walking and risk of prostate cancer–specific mortality and brisk walking appears to be acceptable to men who have undergone radical prostatectomy [8]. Potential mechanisms include reduced levels of circulating insulin, insulin-like growth factor-I (IGF-I), and inflammatory cytokines, in turn leading to reduced proliferation and increased apoptosis of prostate cancer cells [9–13]. In addition, a higher body mass index (BMI) is associated with poorer prostate cancer survival rates [14]. A growing body of evidence suggests that physical activity interventions are associated with beneficial outcomes for prostate cancer survivors, such as improved quality of life, reduced fatigue and reduced incontinence [15–17]. Physical activity interventions guided by behaviour change theory [18] and incorporating wearable technology can increase motivation and engagement in physical activity of cancer survivors [19].

Metformin is the first line medication in the glycaemic control of type 2 diabetes [20], but epidemiological studies suggest an inverse association between metformin and risk of prostate and other cancer incidence, biochemical recurrence and mortality [21–23]. It is thought that metformin inhibits cancer cell proliferation via two main mechanisms; directly, through inhibition of the AMPK/mTOR pathway and, indirectly, by lowering systemic insulin levels [21, 24]. Metformin is well tolerated and widely available at a low cost [22, 24].

The Prostate cancer-Exercise and Metformin Trial (Pre-EMpT) is investigating the feasibility of randomising participants diagnosed with localised, or locally advanced, prostate cancer into a 2 × 2 factorial RCT of physical activity and metformin prescription, and assessing whether wrist worn activity trackers increase motivation and improve adherence. The goal is to obtain results that will provide practical information to allow us to develop a larger, fully powered, definitive trial.

## Methods

The methods here will include a description of the COVID-19-related protocol amendments. Pre-EMpT started recruitment in September 2018 and was due to finish in April 2020. In March 2020, recruitment was closed early due to COVID-19, although delivery of the interventions was performed remotely between March and August 2020. A substantial amendment, including amendments to the protocol, was approved by the Health Research Authority (HRA) and Research Ethics Committee (REC) in July 2020.

### Trial design

Pre-EMpT has a multi-level 2 × 2 factorial design. Participants are randomised to both a physical activity level and a metformin level for 6 months. This results in four intervention groups, receipt of (i) both physical activity and metformin; (ii) physical activity only; (iii) metformin only; and (iv) neither intervention, used as the control (reference) group.

### Trial setting and eligibility criteria

Pre-EMpT is being conducted within a large tertiary referral centre in the South West of England. Participants are recruited from urology outpatient clinics. The inclusion criteria are:Localised or locally advanced prostate cancerDue to undergo external beam radiotherapy/brachytherapy or radical prostatectomy, or due to begin the active surveillance pathwayDue to receive treatment within the recruiting NHS trustCapacity to consent for themselvesAged 18 or overHave sufficient understanding of the English languageNo contraindication to metformin

Exclusion criteria are the following:Inability to give informed consent or unavailability for follow-upBeing identified as unsuitable to participate by their clinicianCurrently taking metformin or insulinCo-morbidities which could prevent metformin prescriptionA physical restriction which would prevent brisk walking

### Consent procedures

This trial employs a 3-part consent process. In the first part (initial consent), participants are consented and randomised over the telephone before their first research clinic appointment so that suitability for metformin can be reviewed and, if not contraindicated, a prescription prepared and dispensed (where necessary) to the research nurse in advance. In the second part (main consent), written informed consent is obtained from each participant when they attend their baseline research clinic appointment. The consent form contains optional clauses to allow the research team to re-contact the participants in relation to further related research, and for their blood and prostate samples to be stored for future (currently unspecified) research purposes. In the third part (interview consent), a proportion of participants are asked to consent to take part in an interview following completion of the active element of the trial after 6 months follow-up.

### Randomisation and blinding

Randomisation will be stratified by treatment group (i.e. external beam radiotherapy/brachytherapy, radical prostatectomy and active surveillance). The research nurse will randomise participants after initial consent, but before main consent, using Research Electronic Data Capture (REDCap, [25, 26]) (a secure web-based system). The research nurse enters the new sequential participant ID and REDCap generates an intervention group for the new participant. This ensures allocation concealment from the nurses who assign participants to the intervention groups.

Participants, and the research team, are not blinded to the intervention allocation. Only those carrying out the analysis are blind to the intervention allocation.

### Interventions

#### Physical activity intervention

Participants allocated to the physical activity group are instructed to walk at a brisk pace for 30 min, on at least 5 days a week, on top of normal physical activity, with the additional aim to walk 10,000 steps every day. They are provided with a waist worn pedometer and a wrist worn Garmin ‘Vivofit 4’ activity monitor. Both the pedometer and Garmin activity monitor will be worn throughout the 6 months duration of the brisk walk intervention. The pedometers measure the number of steps and will be worn throughout the day. The Garmin monitors will be worn day and night and measure number of steps, minutes of moderate physical activity and sleep, and provide movement reminders when an individual has been sedentary for an hour. They can be set to celebrate personalised activity goals and data are available for the individual to view on a smart phone or desktop computer for live feedback. Participants will be asked to record their daily step count for 1 week at baseline, 3, 6, and 12 months follow-up. Physical activity intensity will be recorded by the Garmin activity monitor.

COVID-19 contingency: Participants allocated to brisk walk as part of their intervention will be offered the option of home-based exercises if they are unable, or feel uncomfortable with, brisk walking outside due to COVID-19. Participants will be informed of these exercises via a letter, which will include a 10-min steps workout routine to conduct indoors. This exercise routine is designed to be of similar intensity to brisk walking and safe to perform at home. Participants will be advised that these exercises can be repeated three times a day (30 min in total).

#### Metformin intervention

Participants randomised to the metformin group are prescribed 500 mg slow release metformin per day with food. The tablets are provided at the research clinic visits (baseline and 3 months follow-up).

####  Physical activity and metformin intervention

Participants randomised to the physical activity and metformin group perform both the brisk walking and metformin interventions (as described above) over the 6 months intervention period.

#### Control group

Participants randomised to the control group are asked to carry on with normal levels of physical activity. If participants ask for physical activity advice, standard, publicly available, information would be provided as per usual care.

These participants are not prescribed a placebo for metformin. This study is not designed to test the efficacy of the interventions compared to the control group.

### Strategies to improve adherence to interventions

Participant-facing documents, including the intervention instructions, will be developed in line with the Theory of Planned Behaviour (TPB) [27]. The TPB explores three constructs which predict whether an individual will make a behaviour change or not. These constructs include (1) behavioural beliefs, which produce an attitude towards the behaviour; (2) normative beliefs, which affect perceived social pressure (social norms), and (3) control beliefs which give rise to perceived behavioural control. These constructs come together to influence intention to change behaviour, which can result in change in the actual behaviour. The Garmin activity monitors will also be used as a motivational tool to increase adherence to the brisk walking intervention. These monitors vibrate and display a message when the daily goal of 10,000 steps or weekly goal of 150 moderate intensity minutes is reached, as well as vibrating to notify sedentary activity.

### Harms and provisions for post-trial care

Participants will be informed of the potential risks associated with the interventions before consenting to the trial. These risks include trips or falls and light muscle strain from brisk walking and nausea, diarrhoea, abdominal pain, appetite loss, and taste disturbance from taking metformin. There is no compensation for trial participation.

### Primary and secondary outcomes

Table 1 indicates when each of the primary and secondary outcomes will be collected.

**Table 1 Tab1:** Pre-EMpT data collection

		Study period						
	Pre-trial	Allocation	Post-allocation					
			RC1		RC2		RC3	
Timepoint		0	~ 3 weeks	~ 9 weeks^a^	3 months	~ 14 weeks^b^	6 months	12 months
**Enrolment:**								
Eligibility screen	x							
Randomisation consent		x						
Informed consent			x					
Interview consent							x	
**Assessments:**								
Demographic data			x		x		x	x
Family medical history			x		x		x	x
Height (cm)			x					
Weight (kg)			x		x		x	
Blood sample			x		(x)		x	
Leisure time physical activity [28]			x		x		x	x
Urinary symptoms [29]			x	x	x		x	x
Psychological factors [30, 31]			x		x		x	x
Patient function and bother [32]			x		x		x	x
Health beliefs [adapted from [33, 34]			x		x		x	x
Quality of life measures [35]			x		x		x	x
Cancer-related fatigue [36, 37]			x		x	x	x	x
Lifestyle behaviours (drinking and smoking)			x		x		x	x
Prostate tissue			[x]					
Step count (pedometer)			x		x		x	x
Physical activity intensity/step count (Garmin)			x		x		x	
Metformin tablet count			x		x		x	
Qualitative interview							x	

*RC* research clinic, *[x]* = collected during surgery 1-week post-baseline; *(x)* = metformin groups only

^a^Surgical participants only

^b^Radiotherapy participants only

#### Primary outcomes

Randomisation rate, calculated as the proportion of eligible participants who agree to be randomised for each treatment group. A randomisation rate of 20% or more will be used to determine the feasibility of this outcome.Adherence to the physical activity intervention at 6 months follow-up, assessed via step count recorded by the pedometer for a 1-week period. An adherence rate of 50% or more will be used to determine the feasibility of this intervention based on the same brisk walking intervention in a previously published trial [38].Adherence to the metformin supplementation intervention at 6 months follow-up, measured by tablet count, based on subtracting the number of pills returned at the research clinic visit from the number of pills dispensed. An adherence rate of 60% or more will be used to determine the feasibility of this intervention based on adherence to a nutritional supplementation intervention in a previously published trial [38].

#### Secondary outcomes

 Feasibility of assessing physical activity levels (self-reported at baseline, 3, 6, and 12 months follow-up and based on the Godin Exercise Leisure-time Questionnaire [28]);Intervention tolerability (qualitatively collected data, reporting of adverse events);Trial retention (number of participants successfully followed-up at the end of the 6 months active intervention element of the trial, as a proportion of those who we recruited to the trial and randomised into a study group at the start of the trial);Feasibility of measuring prostate specific antigen (PSA) level (measured at baseline and 6-months follow-up, collected via blood sample);Feasibility of measuring insulin-like growth factor I (IGF-I) (measured at baseline and 6-months follow-up, collected via blood sample);Feasibility of demonstrating methylation and gene expression profiles in blood (measured via blood and tissue (prostate tissue removed during surgery) as part of standard care) samples at baseline and 6 months follow-up);Urinary symptoms (collected at baseline, 3, 6, and 12 months follow-up and based on the International Continence Society male–Short Form, (ICSmale-SF) [29], and additionally collected at 7 weeks following main consent for participants undergoing surgery);Psychological factors (collected at baseline, 3, 6, and 12 months follow-up and based on the Profile of Mood States (POMS) [30] and Benefit Finding Scale [31]);Patient function and bother after prostate cancer treatment (collected at baseline, 3, 6, and 12 months follow-up and based on the Expanded Prostate Cancer Index Composite (EPIC-26) [32]);Health beliefs (collected at baseline, 3, 6, and 12 months follow-up and based on questionnaires measuring constructs of the transtheoretical model of health behaviour change (i.e. stages of change) [33] and the Theory of Planned Behaviour [34]);Quality of life measures (collected at baseline, 3, 6, and 12 months follow-up and based on the Functional Assessment of Cancer Therapy–Prostate (FACT-P) [35]);Cancer-related fatigue (collected at baseline, 3, 6, and 12 months follow-up and based on the Functional Assessment of Chronic Illness Therapy-Fatigue (FACIT-Fatigue) [36] and the EuroQol 5 dimensions questionnaire (EQ-5D-5L) [37], additionally collected at 4.5 months after main consent for participants undergoing external bean radiotherapy or brachytherapy);General lifestyle factors (self-reported levels of smoking and drinking); Feasibility of participants with localised prostate cancer wearing wrist worn activity trackers (assessed by qualitative interview and the 7 day monitoring form); Impact of wrist worn activity trackers on adherence to the physical activity intervention (assessed by step count on the 7 day monitoring form and data recorded by wrist worn activity trackers);Weight and body mass index (measured by a nurse);Attitudes and views of participants about the physical activity and metformin interventions and participation within the trial (based on qualitative interviews conducted once participants complete 6-months follow-up).

Participants are given the opportunity to complete all questionnaires electronically if they would prefer via a secure online questionnaire system, RedCap.

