### Research clinic 1: baseline

At the initial research clinic appointment, informed consent is re-confirmed, and the consent form is signed. Baseline data are collected, based on all the outcome measures to be collected at follow-up. Participants are informed of their intervention group and provided with specific intervention group instructions.

The research nurse ensures that the participants know how to carry out their interventions. Participants in the metformin group are seen briefly by a urologist and provided with 3 months medication. All participants are provided with a pedometer to wear continuously for the 6 months duration of the trial. In addition, participants in the physical activity intervention are provided with a Garmin ‘Vivofit 4’ activity tracker to wear for the 6 months duration of the trial intervention. All participants will be given a 7 day monitoring form where they log their daily step count over 1 week and, where appropriate, whether they have completed 10,000 steps, achieved the target brisk walking and taken their metformin tablet. This monitoring form is returned to the trial team by post.

Following baseline research appointment, a letter is sent to the participants’ GP, informing them that their patient is participating in the research trial and letting them know which intervention group they are in.

Approximately 6 weeks after surgery, participants undergoing radical prostatectomy receive an additional urinary symptom questionnaire.

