### Analysis plan

The primary comparative analyses are by intention-to-treat for randomisation rates and adherence to treatment. Baseline characteristics for each group are tabulated using means and standard deviations for normally distributed data, medians and interquartile ranges for non-normally distributed data, and percentages and counts for categorical data. Outcome measures at baseline and follow-up are tabulated to assess the range of values to inform sample size calculations for a definitive trial. Secondary outcomes are tabulated as described above.

The measures made on the tissue and blood samples are research measures and do not have any direct clinical relevance for the participant or their routine clinic treatment. Analysis includes mean serum, plasma, and tissue levels of components of the IGF axis, including IGF-I as a biomarker of prostate cancer progression, and PSA level. Concentrations of IGF-I will be measured using gold standard ‘in-house’ radioimmunoassays. PSA levels will be measured using standard methods employed by the study’s NHS Pathology laboratory. Bloods and tissue may also be analysed for genetic, epigenetic, and metabolomic biomarkers.

Semi-structured face-to-face or telephone interviews will be conducted with participants to explore their experiences of their allocated intervention and the trial generally. Purposive sampling will be used to recruit up to 5 participants from each of the interventions, who underwent different treatment types and who wore the wearable activity tracker. The interviews will be audio-recorded, transcribed, anonymised, and analysed thematically using a qualitative method. A qualitative analysis computer program, such as NVivo [39], will be used to assist with the analysis.

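### Feasibility of wearing the wrist tracker is assessed from interviews and a form that, as described, cannot give a wear rate, while the tracker data already scheduled are not named for this outcome

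*Protocol article*

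**What the plan says.** Four parts of the protocol article bear on this outcome.

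- **Secondary outcomes.** The outcome is whether wearing the wrist tracker is feasible for these men, "assessed by qualitative interview and the 7 day monitoring form". No other source is named. The next outcome in the list, the tracker's impact on adherence, draws on the form's step count and also on data recorded by the tracker.
- **Research clinic 1: baseline.** On the form: "All participants will be given a 7 day monitoring form where they log their daily step count over 1 week". Where applicable, men also record "whether they have completed 10,000 steps, achieved the target brisk walking and taken their metformin tablet". On the step device: "All participants are provided with a pedometer to wear continuously for the 6 months duration of the trial". Only men allocated to physical activity also receive the tracker.
- **Physical activity intervention and Table 1.** "The Garmin monitors will be worn day and night and measure number of steps, minutes of moderate physical activity and sleep". Table 1 schedules Garmin intensity and step data at the baseline, 3-month and 6-month clinics. Pedometer step count is scheduled at those times and also at 12 months.
- **Analysis plan.** Interviewees are sampled purposively, up to 5 from each intervention, "who underwent different treatment types and who wore the wearable activity tracker".

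**The concern.** The natural summary of whether men will wear a device day and night for 6 months is a wear rate among those issued with it. Neither named source is described in a way that produces one. A man who stops wearing the tracker can still complete every listed item on the form, using his pedometer for the steps. The interview criterion, read literally, starts from men who wore the device, so it may over-represent wearers in an outcome that is about wearing.

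The stake is moderate. The Background makes the effect of wrist trackers on motivation and adherence part of the trial's purpose, and the adherence strategy relies on the tracker as a motivational tool. An effect on adherence is hard to interpret without knowing how many men wore the device and for how long. That figure is also practical information a definitive trial would want.

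**Working it through.** The article states no figure for tracker wear, so there is nothing to reproduce. The check compares passages and adds a small calculation of scale.

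**1. Does the form record wear?** The listed items are daily steps, 10,000 steps reached, brisk walking done and tablet taken. Wear is not among them.

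**2. Does a completed form imply wear?** No, for three reasons.
- All participants receive the form, including the two groups given no tracker, who must take their steps from the pedometer.
- The primary adherence outcome takes its one-week step count from the pedometer.
- The form is used again at 12 months, whereas trackers are handed back at about 6 months.

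**3. How much of the wear period could the form cover, even with a wear item?** It covers one week at each of baseline, 3, 6 and 12 months. The 12-month week falls after the tracker is returned. That leaves about 3 weeks out of roughly 26 in the intervention period.

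**4. How many tracker men can the interviews reach?** The allocation ratio is not stated, so equal allocation to the four groups is assumed.
- Men issued a tracker: 122/2 = 61 as planned, or 110/2 = 55 as recruited.
- Interviews, counting the two physical activity groups as two interventions: at most 2 × 5 = 10. That is 10/61 = 16% or 10/55 = 18%.
- Interviews, counting brisk walking as one intervention: at most 5. That is 5/61 = 8% or 5/55 = 9%.

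For the remaining tracker men, the form is the only source named for this outcome.

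**5. Is there a better source already in the plan?** Yes. Tracker data are scheduled at three clinics, and the adjacent outcome already uses them. If every man issued a tracker were in the denominator, the 95% half-width for a wear proportion, at its widest (50%), would be:
- 1.96 × √(0.25/61) = 12.5 percentage points with 61 men;
- 1.96 × √(0.25/55) = 13.2 percentage points with 55 men.

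That is adequate for a feasibility estimate.

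**6. Is the sampling sentence coherent?** It draws from each of the interventions and adds tracker-wearing as a criterion. Men on metformin alone receive no tracker, so the criterion cannot apply to them. The same holds for the control group if it is included.

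**The case against.** The strongest reply is that the trial does collect what is needed. Garmin data are scheduled at baseline, 3 and 6 months, and a man who took the device off early should show as absent or sparse data. A reader might infer that non-wear cannot be detected in this trial, or that the men not interviewed (at least 45 of 55, 82%) have no wear information. The documents do not support either inference, because both ignore the scheduled device data. What stands is that those data are not named for this outcome.

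A reader might also infer that interviews are restricted to wearers, so that the result can only be favourable. This is not supported either. A strict wearers-only rule conflicts with sampling from each intervention in the same sentence. The phrase may be a variation criterion, or may simply mean men issued a tracker. Interviewees could in any case report discomfort, partial wear or stopping. What stands is that the wording is ambiguous and may favour wearers.

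Two further points have weight. The article may condense the form, which is not shown and could carry a wear item; even then, self-report would cover only about 3 weeks. The outcome is also one of many secondary outcomes and has no threshold. The Discussion ties progression to the primary outcomes, and the primary walking measure uses the pedometer. This limits the consequence but does not make the named sources suitable.

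**Conclusion.** The point holds as a gap in how one secondary outcome is defined. The interview and the form, as described, cannot give a wear rate, and the device data that could are assigned only to the neighbouring outcome. The interviews reach at most 16% to 18% of men issued a tracker, or 8% to 9% if brisk walking counts as a single intervention.

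These percentages assume equal allocation. The statement about the form assumes that the article's list of its contents is complete. The gap does not touch the primary outcomes or the stated progression criteria. It is worth correcting because the better source is already scheduled for collection.

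**What to change.** - **Main source.** Name device-recorded wear for this outcome. Examples are the proportion of men issued a tracker who have recorded data, or the number of days with data, at 3 and 6 months. The article does not say how long a period the downloads cover, so the definition should use whatever period they provide and should not presume continuous daily logs over 6 months.
- **Denominator and missing data.** Use all men issued a tracker. Report missing device data separately by reason where known (withdrawal, lost device, failed sync), and add a sensitivity analysis that counts missing as non-wear.
- **Supporting information.** Keep the interviews and the form. In the sampling sentence, change 'wore' to 'were given' and limit that criterion to the physical activity groups, so that men who stopped wearing the tracker can be interviewed.

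The cost is a change of outcome wording and a little extra data processing, with no added burden on participants. The downside is that some missing device data will not reflect true non-wear, which is why the reasons and the sensitivity analysis are needed. Recruitment closed in March 2020, so the sampling change may come too late for some or all men. The change of source depends only on data already scheduled.

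### The listed tracker effect on walking adherence cannot be estimated, because every participant allocated to walking is given a tracker and no walking group or period without one is described

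*Protocol article*

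**What the plan says.** The aim appears at the end of the Background, where the trial is described as "assessing whether wrist worn activity trackers increase motivation and improve adherence". Secondary outcomes then lists "Impact of wrist worn activity trackers on adherence to the physical activity intervention", to be "assessed by step count on the 7 day monitoring form and data recorded by wrist worn activity trackers". The item just before it separately covers the feasibility of wearing trackers, so this one is additional and is worded as an effect.

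On allocation, Trial design says: "Participants are randomised to both a physical activity level and a metformin level for 6 months". The tracker is not a randomised factor.

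On who receives the device, the Physical activity intervention section says of the walking group: "They are provided with a waist worn pedometer and a wrist worn Garmin". The section on Research clinic 1 says "All participants are provided with a pedometer to wear continuously for the 6 months duration of the trial", and then "In addition, participants in the physical activity intervention are provided with a Garmin" tracker. No tracker is described for the metformin-only or control groups. Both devices are to be worn for the full 6 months of the walking intervention.

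The section on strategies to improve adherence makes the tracker one of the means of raising walking adherence. The Analysis plan says only that secondary outcomes are tabulated, and describes no tracker comparison.

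**The concern.** To say that a tracker improves adherence is to compare adherence with it and adherence without it, in people asked to do the same walking. The described design contains only the first of these. The two stated measures do not supply the second: step counts on the 7 day form show how much people walked, and Garmin data exist only for people given a Garmin.

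What is at stake is the reading of one stated aim and one listed outcome. The trial exists to inform a definitive trial. If walking adherence turns out well, an outcome labelled as the tracker's impact invites the inference that the device produced it, when the walking instruction, the step goal and the supporting materials came with it.

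**Working it through.** The plan gives no figure for this outcome, so there is none to reproduce. The check is whether the effect can be identified.

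**1. Tracker provision by randomised group** (Trial design; Physical activity intervention; Research clinic 1)

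| Group | Walking (W) | Metformin (M) | Tracker provided (T) |
|---|---|---|---|
| Walking and metformin | 1 | 1 | 1 |
| Walking only | 1 | 0 | 1 |
| Metformin only | 0 | 1 | 0 |
| Neither | 0 | 0 | 0 |

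T = W in every row.

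**2. Identifiability.** With columns for intercept, W, M and T, the design matrix over the four groups has rank 3 for 4 columns, so W and T cannot be separated. Adherence to walking is defined only in the walking groups. There T is always 1, and the columns intercept, M and T have rank 2 for 3 columns. More participants would not change either result.

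**3. Size of the comparison.** The article states no allocation ratio. Assuming half are allocated to walking:
- Planned: 122/2 = 61 with a tracker, 0 without.
- Recruited: 110/2 = 55 with a tracker, 0 without.

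Another ratio would change 61 and 55 but not the zero.

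**4. Could another contrast in the document supply the missing group?**
- *Walking versus non-walking groups.* This mixes the tracker with the walking instruction and the 10,000-step goal, and non-walkers have no walking intervention to adhere to.
- *Before versus after.* The tracker is issued at the same clinic visit as the walking instructions. It is returned at 6 months, and the 12-month data come 6 months after the intervention has ended. No period has walking prescribed without the tracker.
- *More versus less frequent wearers.* This is not planned and not randomised, and wearing the device is itself a sign of motivation.
- *The 50% adherence threshold in Primary outcomes.* It is based on an earlier trial of the same walking intervention, but it serves as a feasibility criterion. No tracker comparison against it is planned, and the article does not say whether that trial used trackers.
- *Interviews.* They can describe perceived motivation, but not a difference in step-count adherence.

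**5. What randomising the tracker would have given at this size (illustration).** Assume equal allocation to walking, a 1:1 tracker split within walking, and 50% adherence without a tracker. The 95% half-width for the difference is 1.96 × √(2 × 0.25/n), with n per subgroup:
- 122 participants: n = 61/2 = 30.5; 1.96 × √(0.5/30.5) = 0.251, about ±25 percentage points.
- 110 participants: n = 55/2 = 27.5; 1.96 × √(0.5/27.5) = 0.264, about ±26 points.

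At 122 participants, power to detect gains of 10, 20 and 30 points would be about 12%, 35% and 70%. Reaching 80% power would take 388, 93 and 39 per subgroup. A split would have made the effect estimable but imprecise, so the question belongs in a later trial.

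**The case against.** The strongest reply is that nothing in the plan commits the investigators to a causal analysis. Secondary outcomes are tabulated, no tracker contrast or test is described, and the article disclaims power for efficacy and says the study is not designed to test efficacy against control. The tracker is openly part of the walking package, so adherence to that package is a coherent feasibility question. Details of reporting may also sit in the full protocol or analysis plan, which are not shown.

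Most of this stands, and it limits the point. A reader might infer any of the following, none of which the document supports:
- *Reporting as planned would credit the tracker with the adherence achieved.* Tabulation makes no such claim; the risk lies in how a table under that label is read.
- *The decision to proceed is compromised.* The Discussion ties progression to the primary outcomes, and none of them requires the tracker to be separated from the walking package.
- *No control wears a tracker.* The article says only who is provided with one and is silent on personal devices.
- *The whole tracker aim is unanswerable.* Perceived motivation can be explored in the planned interviews, and the feasibility of wearing a tracker is a separate, answerable outcome.
- *Pedometers and motivational mailings are part of what distinguishes the walking groups.* Everyone receives a pedometer, and the mailings are not described as limited to walkers.

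What does not stand is the appeal to documents not shown. The difficulty comes from who receives the device, and no analysis plan can repair that. The efficacy disclaimers concern the interventions against control and do not withdraw the tracker aim.

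**Conclusion.** The point holds as a wording error in one aim and one secondary outcome. As described, tracker provision and walking allocation are the same variable, and within the walking groups there is no untracked comparator, so an effect of the tracker on adherence cannot be estimated. This follows from the article's description of provision and rests on no statistical assumption; only the counts of 61 and 55 depend on equal allocation.

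The consequence is modest: a secondary aim that could be over-interpreted when the definitive trial is planned. Randomisation rate, walking adherence and metformin adherence remain assessable as primary outcomes.

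**What to change.** Replace the effect wording in the Background and in Secondary outcomes with descriptive outcomes that use data already scheduled:
- Garmin step and intensity data at baseline, 3 and 6 months;
- attainment of the 10,000-step and brisk-walking goals on the 7 day form;
- agreement between Garmin and pedometer step counts;
- interview views on whether the tracker affected motivation.

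Add a statement that adherence is to the walking package including the tracker, that no causal claim about the tracker will be made, and that testing its effect would require randomising the tracker within the walking arms of a later trial.

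The cost is a change to one aim and one secondary outcome. It needs no new data, so it remains possible although recruitment has closed. The trial gives up only a claim that its design cannot support.
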